### Allocation concealment mechanism

The randomization was performed on a centrally managed database once informed consent was obtained.

### Implementation

The sequence will be generated and forwarded by the computer specialist who created the case report form (CRF) online to implement the online database. By doing so, each investigator can randomize their patients and assign them to the respective group of treatments. The date of randomization will be recorded.

### Blinding (masking)

The blind level was set as double-blind. All patients, doctors, data collectors and analysts will be unaware of the grouping of patients. We do not anticipate any requirement for unblinding but if required, the Trial Manager, Data Coordinator, Implementation Support Facilitators, and Care Home Managers will have access to group allocations and any unblinding will be reported.

### Data collection, management, and analysis

#### Clinical data

Clinical data from patients will be obtained by medical staff and recorded on an online electronic platform (Http://www.medresman.org.cn) and in the CRF table. The sample will be coded, and the patient's identity will be known only by the attending physician. The clinical data will include the following: general patient information, past medical history, past surgical history, laboratory examination results, imaging results, surgery details, postoperative infection rate, incidence of postoperative complications, incidence of anastomotic leakage, and 30-day readmission rate after surgery. The timing and processing of the above-recorded contents will all be reflected in the CRF table, and the laboratory examinations will mainly assess preoperative and postoperative routine blood and inflammatory indicators (Table 2).

**Table 2 Tab2:** CRF table

Stage	Pre-operation		Intra-operation	Post-operation						
Follow-up period	14–3 days	3–1 days		1–14 days	30 days	1–12 months	12–24 months	24–36 months	36–48 months	48–60 months
Baseline data collected	√	-	-	-	-	-	-	-	-	-
Inclusion and exclusion	√	-	-	-	-	-	-	-	-	-
Sign informed consent	√	-	-	-	-	-	-	-	-	-
Group determination	√	-	-	-	-	-	-	-	-	-
Physical examination	√	-	-	-	√	√	√	√	√	√
Imaging examination	√	-	-	-	-	√	√	√	√	√
laboratory examination	√	-	-	-	√	√	√	√	√	√
First administration	-	√	-	-	-	-	-	-	-	-
Administration	-	-	-	√	√	√	√	√	√	√
Postoperation pathology	-	-	-	√	-	-	-	-	-	-
Safety observation	-	-	√	√	√	√	√	√	√	√
Record adverse events	-	-	√	√	√	√	√	√	√	√
Other works	√	√	√	√	√	√	√	√	√	√

A detailed description of the above data is shown in the CRF table.

#### Sample size calculation basis and formula

A larger sample size is required for this study to provide adequate statistical power.

Based on our current known information and two similar clinical studies on recurrence and metastasis of colorectal cancer (1108 patients enrolled in a berberine hydrochloride clinical trial for colorectal adenoma prevention by Ying Xuan Chen et al., Shanghai Renji Hospital, 2014–2016, Lei Huang et al. from the First Affiliated Hospital of Anhui Medical University during the 2015–2020 clinical trial of aspirin to prevent colorectal cancer metastasis were planned to enrol 3000 patients) and combined with feasibility and study length consideration, we determined the sample size to be 300 patients, experimental group: control group = 1:1, that is, 150 patients in the experimental group and 150 patients in the control group.

#### Statistical analysis

The association with the variables of interest will be compared between groups by means of Pearson’s chi-squared test or Fisher’s exact test, as appropriate and in the case of categorical variables. For continuous variables, Student’s *t* test for independent samples and the Mann–Whitney *U* test will be used for normally and nonnormally distributed variables, respectively.

The analysis for the primary end-point variable (incidence of postoperative liver metastasis) will be performed with an intention-to-treat approach. The absolute difference in terms of incidence will be computed, along with 95% confidence intervals, and will be expressed as relative risk or odds ratio, as appropriate for each outcome.

An interim analysis is planned, once 50% of the patients have completed their treatment (half of the patients per arm). The study can be suspended if the treatment superiority is statistically significant, with a *P* value set at <0.0052. The interim analysis will be performed in agreement with previously reported epidemiological and statistical criteria.

For the secondary variables, a similar approach will be used, using the effect estimate with a 95% confidence interval and the relative risk and odds ratio for categorical variables.

Any potential effects related to centres or surgeons will be assessed by means of mixed models. For the primary end-point variable, a bivariate and multivariate analysis will be performed to identify the potential effects of other variables.

The value for statistical significance at the final analysis was set at *P* < 0.05. Statistical analysis will be performed with SPSS 20. All the deviations from the original statistical plan will be described and justified. All subjects included in the study will be included in the analysis.

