
### Interventions

Metronidazole/placebo: Treatment regimens were developed on their own according to each centre’s metronidazole specifications, which required maintenance of metronidazole plasma concentrations for subjects in the experimental group to be > 0.01 μG/ml, and the duration of administration was tentatively set at 5 years (i.e., the time of the outcome of this experiment).

The chemotherapy regimen is eFOLFOX_6_:

Oxaliplatin 85 mg/m^2^ IV infusion for 2 h, D1; leucovorin 400 mg/m^2^ IV for 2 h, D1; fluorouracil 400 mg/m^2^ IV bolus on D1 followed by 1200 mg/m^2^/DX2 continuous IV infusion (total 2400 mg/m^2^ over 46–48 h infusion). This process was repeated every 2 weeks for a total of 24 weeks (Table 1).

**Table 1 Tab1:** Chemotherapy regimen

Drug name	Dose	Timing of the drugs (a total of 28 days/cycle)							
		Pre-operation	Post-operation						
		D3–D1	D1	D2	D3–D14	D15	D16	D17–D21	D22–D28
Metronidazole/placebo	1 g	√	√	√	√	√	√	√	-
Oxaliplatin	85 mg/m^2^		√	-	-	√	-	-	-
Leucovorin	400 mg/m^2^		√	-	-	√	-	-	-
Fluorouracil	400 mg/m^2^		√	-	-	√	-	-	-
Fluorouracil	2400 mg/m^2^(total)		√		-	√		-	-

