### Outcomes

#### Primary outcome

Efficacy will be measured in terms of the incidence of postoperative liver metastasis within 5 years after surgery.

Assessment will be conducted by in-person visits; should the status of the pandemic impact the study with no possibility of performing in-person 5-year follow-up appointments, telemonitoring might be considered using validated tools.

Considering that the dose of metronidazole is predicted in the form of a hypothesis, the incidence of drug-related adverse events will be regarded as one of the main indicators of this study.

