#### Auditing

The project management team will meet once a month to review the progress of the trial. As patients may experience some side effects during long-term administration of metronidazole, the trial steering team at each sub-centre, assigned by the team leader unit, will review the follow-up of subjects at each centre every 2 to 3 months to prevent irreparable harm to patients due to doctors’ or nurses’ errors. The hospital ethics review committees will work together to form an independent data monitoring committee that will review the data from each sub-centre every 3 months and at the time of interim analysis (performed once 50% of the planned sample of patients completed the primary endpoint follow-up )to verify the safety of treatment in both arms.

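### The final level of P < 0.05 is not reduced for the efficacy interim at P < 0.0052, so the overall type I error is about 5.2%, not 5%

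*Protocol article*

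**What the plan says.** The protocol article, under Statistical analysis, plans one interim look: "An interim analysis is planned, once 50% of the patients have completed their treatment (half of the patients per arm"). It attaches an efficacy rule to that look: "The study can be suspended if the treatment superiority is statistically significant, with a *P* value set at <0.0052". For the end of the trial it says: "The value for statistical significance at the final analysis was set at *P* < 0.05". It gives no reduced final level, and it does not state an overall alpha or whether the tests are one- or two-sided.

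The Auditing section times the interim differently, as "performed once 50% of the planned sample of patients completed the primary endpoint follow-up", and describes the monitoring committee's task at that point as checking safety.

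Two other sections bear on the timing. Interventions says "the duration of administration was tentatively set at 5 years (i.e., the time of the outcome of this experiment"), and Primary outcome defines the endpoint as "incidence of postoperative liver metastasis within 5 years after surgery".

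**The concern.** A trial that may claim superiority at an interim look and again at the end has two chances of a false positive result. To hold 5% overall, the final level must give back what the interim spent. Here the interim level looks like one half of a matched O'Brien-Fleming pair, while the final level is the one that would apply had there been no interim.

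Both values are stated, so this is not a detail left to an unseen analysis plan. An analysis plan that used a reduced final level would contradict this text. At stake is the claim on the primary endpoint when the final P value falls just under 0.05.

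**Working it through.** **Inputs.** Interim level 0.0052 and final level 0.05 (Statistical analysis). Information fraction t = 0.5, from the trigger of half the patients. Sample size: "150 patients in the experimental group and 150 patients in the control group", so 75 per arm at a 50% interim. Test: "Pearson’s chi-squared test or Fisher’s exact test, as appropriate and in the case of categorical variables". Two-sided testing and a 5% overall level are assumed, inferred from the 0.05 level and the 95% confidence intervals.

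**Model.** Under no treatment effect, the interim statistic Z1 and final statistic Z2 are bivariate standard normal with correlation √t = √0.5 = 0.707. The overall error is P(|Z1| > c1 or |Z2| > c2).

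**Step 1: reproduce the plan's interim figure.** A two-look O'Brien-Fleming design has c1 = C√2 and c2 = C. Solving for an overall 0.05 gives C = 1.9774.
- Interim: c1 = 1.9774 × 1.4142 = 2.797, nominal P = 0.00517, which rounds to the stated 0.0052.
- Final: c2 = 1.977, nominal P = 0.0480.

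**Step 2: the pair as written.** For 0.0052, c1 = 2.794. For 0.05, c2 = 1.960.
- P(|Z1| > 2.794) + P(|Z2| > 1.960) = 0.0052 + 0.0500 = 0.0552.
- Probability that both are exceeded: 0.0032.
- Overall error: 0.0552 − 0.0032 = 0.0520. A simulation of 5 million normal pairs gave 0.0518.

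**Step 3: other readings.**
- Interim stop in the benefit direction only: the interim adds half of 0.0020, so 0.0510.
- Both levels read as one-sided: 0.0516, against a one-sided 0.05.
- Binomial simulation with Pearson's test, 75 then 150 per arm, with assumed true rates in both arms:

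| Assumed rate | Final test alone | Two looks as written |
|---|---|---|
| 15% | 0.0496 | 0.0514 |
| 20% | 0.0500 | 0.0518 |
| 25% | 0.0504 | 0.0521 |

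**Step 4: dependence on the information fraction**, with 0.0052 held fixed.

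| t | Overall error as written | Final level that restores 0.05 |
|---|---|---|
| 0.3 | 0.0532 | 0.0467 |
| 0.5 | 0.0520 | 0.0480 |
| 0.7 | 0.0508 | 0.0492 |
| 0.8 | 0.0503 | 0.0497 |
| 0.9 | 0.0500 | 0.0500 |

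**Step 5: can it change a conclusion?** With 150 per arm and Pearson's test without continuity correction, 33 against 20 liver metastases (22.0% against 13.3%) gives P = 0.0491. That is significant as written but not at 0.048. The 22% lies within the 15 to 25% postoperative incidence given in the Introduction.

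**Step 6: the trigger.** Statistical analysis counts completed treatment and Auditing counts completed primary-endpoint follow-up. Interventions equates the 5-year treatment period with the time of the outcome, so the two nearly coincide for patients who stay on study drug. They part for patients who stop early, and would part further if the tentative duration changed.

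**The case against.** The strongest objection is size. The excess is 0.2 percentage points in the base case and 0.1 if only benefit-direction stops count, which is the natural reading of a rule about superiority. The stopping rule is also permissive, so 5.2% assumes that every interim crossing is claimed as a success. At high information fractions the excess all but vanishes. All of this stands, and it limits the severity. It does not remove the mismatch, because every two-look reading at the planned half-way point exceeds 5%.

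The value 0.048 is tied to 50% information, and the protocol article fixes only a count of patients. If the interim also used partial follow-up on later patients, the fraction could be higher. That stands too, so the fix has to be conditional.

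A reader might infer from the completed-treatment trigger that the superiority decision would rest on an adherence-selected subset. The documents do not support this. The trigger says when the look happens, not who is analysed, and it requires half of the patients in each arm. The same section specifies intention-to-treat for the primary endpoint and includes all subjects in the analysis. The Introduction keeps patients discontinued for drug reactions in the intention-to-treat set.

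A reader might also infer that the look comes too late to spare much treatment. That depends on an accrual period that the protocol article does not give, and whether to keep the look is a design choice rather than an error.

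**Conclusion.** The point holds as a small but real error in the primary decision rule. The interim level is half of a matched pair, and the other half was replaced by an unadjusted 0.05. Overall two-sided type I error is about 5.2% at 50% information, about 5.1% counting benefit-direction stops only, and between 5.3% and 5.0% for fractions of 30% to 90%. Only a final P between 0.048 and 0.05 would change the conclusion at 50% information.

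This rests on two-sided testing at an intended overall 5%, on an interim crossing leading to an efficacy claim, and on the normal approximation, which the binomial simulations support. The differing trigger wording is a minor matter of harmonisation. Overall this should be fixed. It does not show that the trial's error control is seriously compromised.

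**What to change.** - **Final level.** Under Statistical analysis, replace the final level by P < 0.048, paired with the stated 0.0052, on condition that the interim uses 50% of the primary-endpoint information. State the two-sided overall 5% level explicitly.
- **Other fractions.** If the actual fraction differs, compute the final level from an O'Brien-Fleming-type spending function at that fraction. A spending function sets the interim and final levels together, so 0.0052 would then be recomputed as well. If 0.0052 is instead kept fixed, the table in the working gives the matching final level.
- **Trigger.** Use one trigger under both Statistical analysis and Auditing: half of all randomised patients have reached the primary-endpoint time, counting those off study drug.

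The cost is a few sentences and a slightly stricter final threshold (critical value 1.977 instead of 1.960), with negligible loss of power. The change should be made before the interim data are seen, so that it cannot appear data-driven.

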### Safety

Adverse events refer to adverse medical events that occur in clinical trial patients after receiving medications. In this study, an adverse event will be considered regardless of whether it is related to the therapy from the time when patients sign the informed consent form to 1 month after the end of treatment. Assessing the nature and determining the severity of adverse events will be conducted in accordance with “expert consensus on diagnostic criteria for postoperative complications of gastrointestinal cancer in China”. To assess the adverse events and their causal relationship to therapy, the investigator will evaluate the possible associations between adverse events and trial medications. The following five criteria will be used to determine the results: the time of occurrence of adverse events coincides with the time of administration, adverse events are related to known adverse reactions of the medication, adverse events cannot be explained by other reasons, adverse events disappear after discontinuing therapy and adverse events are reproduced after medication administration. The results documented as positive, relevant and possibly related were deemed to be adverse reactions. The incidence of adverse reactions will be calculated accordingly. To record, process and report adverse events, the investigator will document any adverse events. Records of adverse events will include a description of adverse events and all related symptoms, time of occurrence, severity, duration, measures taken, the results and final outcomes. The reporting methods and treatment measures for severe adverse events will be classified as severe adverse events if they meet one or more of the following criteria: death, life-threatening (e.g., immediate risk of death), prolonged hospitalization or hospitalization, permanent or severe disability, congenital malformations or defects, some events that have not yet caused death, danger to life or hospitalization but will consider a severe adverse event by a physician if they cause harm to the patient or require medication or surgical treatment to avoid the above situation. For any severe adverse events during the clinical trial, the investigator will file a report of severe adverse events within 24 h and report in writing to the Ethics Committee, the superior authorities and the sponsor. The written report will include the time, severity, duration, measures taken and outcomes of serious adverse events.

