The long-term effects of metronidazole use cause serious side effects and have been reported as individual cases in recent years. The probability of developing peripheral neuropathy in patients who continue to take metronidazole for > 4 weeks (taking a total dose of > 42 g) for a long period of time is approximately 17.9% [11, 12]. According to calculations, the blood concentration is approximately 34–45 μg/ml when patients develop peripheral neuropathy, and nearly all patients experience symptom resolution after discontinuing the medication. Therefore, for this study, we set the duration of metronidazole administration to 5 years in our patients, and because anaerobes are extremely sensitive to metronidazole, the dosage was extremely low, and in addition to long-term regulatory follow-up, patients in this protocol only needed to maintain daily blood concentrations greater than 0.01 μG/ml, which can maximize patient safety. At the same time, all the studies with patients who showed drug-related adverse reactions were discontinued, which was included in the ITT set and not included in the PP set.

The aim of this prospective, single-centre, large sample, randomized controlled trial is to demonstrate that long-term oral antibiotics can effectively reduce the incidence of post-operative liver metastasis in patients with colorectal cancer. Secondary objectives included safety and acceptability of the drugs used, treatment-related morbidity and mortality, and relevant follow-up.

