#### Secondary outcomes

Postoperative complication rates: Postoperative complications will be classified according to their impact and the required management (e.g., medical treatment, reoperation, drainage), as proposed by Clavien–Dindo. Complications will be assessed at the 30-day follow-up; ancillary studies will assess complications at the 60-day and 5-year follow-ups. The Cumulative Complication Index will also be computed to assess the global burden of complications on each patient.Complete postoperative recovery: number of days between admission and when the patient is suitable for discharge.Unplanned secondary surgeryReadmission: need for any unplanned readmission after discharge for any reason.1-year, 3-year and 5-year survival ratesRelapse-free survival (RFS)Overall survival (OS)

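### Adverse events of a tentative five-year oral drug course are classified and graded with a consensus whose title covers only postoperative complications, and no drug-toxicity scale is named

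*Protocol article*

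**What the plan says.** The Safety section of the protocol article sets one standard for both the type and the grade of adverse events. Its sentence opens with their nature and continues: "determining the severity of adverse events will be conducted in accordance with “expert consensus on diagnostic criteria for postoperative complications of gastrointestinal cancer in China". Events count whether or not they are related to therapy, and the collection window runs "from the time when patients sign the informed consent form to 1 month after the end of treatment". Under Interventions, "the duration of administration was tentatively set at 5 years".

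Three other places bear on this:

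- The Primary outcome section gives drug harm a prominent role: "the incidence of drug-related adverse events will be regarded as one of the main indicators of this study".
- The Introduction names one specific metronidazole toxicity and gives it a rate: "The probability of developing peripheral neuropathy in patients who continue to take metronidazole for > 4 weeks" (more than 42 g in total) is put at approximately 17.9%.
- The Secondary outcomes section handles surgical complications separately: "Postoperative complications will be classified according to their impact and the required management", following Clavien–Dindo, with the main assessment at 30 days and ancillary assessments at 60 days and 5 years.

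The Safety section also lists five criteria for causality and a set of criteria for severe (in effect, serious) events. The document names no scale for drug toxicity.

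**The concern.** The instrument and the events do not match in scope. A consensus on diagnosing complications of gastrointestinal cancer surgery is, by its title, about what follows an operation. Most of the observation window concerns an oral drug taken for years, and the one specific metronidazole harm that the plan names is neurological and linked to duration and cumulative dose, not to surgery. An investigator who follows the Safety section and sees a patient with paraesthesia in year 2 is directed to surgical criteria for both the event term and its grade.

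What is at stake is consistency. If the named standard has no fitting definition or grade for such an event, investigators will improvise, and one investigator's mild event will be another's moderate. Blinding should keep this from favouring either arm systematically, but it blurs any comparison of severity and makes it harder to say whether long-term metronidazole is tolerable. The Primary outcome section itself says that the dose rests on a hypothesis, so tolerability is something the trial is meant to establish. The data monitoring committee's 3-monthly safety review (Auditing section) would work from the same grades.

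**Working it through.** The plan states no figure on this point that could be reproduced, so the check is a comparison of sections, with simple arithmetic for scale.

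**1. Which tool does which job**

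| Task | Tool named in the protocol article | Fits late drug toxicity? |
|---|---|---|
| Nature of the adverse event | Consensus on postoperative complications (Safety) | Not by its title |
| Severity of the adverse event | Same consensus (Safety) | Not by its title |
| Causality | Five criteria (Safety) | Yes, but they define and grade nothing |
| Seriousness | List of criteria (Safety) | Yes, but it is a yes/no reporting threshold with no grade for non-serious events |
| Surgical complications | Clavien–Dindo (Secondary outcomes) | Not intended for it |

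Drug toxicity therefore has rules for causality and seriousness. For event definition and grade it has only the surgical consensus.

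**2. Length of the window**

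Inputs: 5 years of treatment (Interventions, tentative) and 1 month after the end of treatment (Safety). Then 5 × 12 + 1 = 61 months, plus the short preoperative period after consent. Table 2 agrees: adverse events are recorded in every column from the operation to 48–60 months.

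**3. Does the main indicator depend on the grade?**

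The indicator is the incidence of drug-related adverse events. The Safety section counts an event as an adverse reaction according to the causality judgement and computes the incidence from that count. The grade does not enter, so the incidence can be calculated as the plan stands. The only link to the incidence is indirect: the consensus also governs the nature of events, so an ill-fitting set of definitions could affect how an event is recognised and coded.

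**4. Scale of the named toxicity**

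Inputs: 17.9% (Introduction) and 150 patients in the experimental group (sample size section).

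- At the cited rate: 150 × 0.179 = 26.9, about 27 patients.
- At one tenth of that rate, as a sensitivity value: 150 × 0.0179 = 2.7, about 3 patients.

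The first figure assumes that the cited rate applies to this regimen. The Introduction argues otherwise: it associates neuropathy with blood concentrations of about 34–45 μg/ml, while this protocol requires only more than 0.01 μg/ml.

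The documents do not settle the actual exposure. Table 1 shows 1 g on 3 preoperative days and on days 1 to 21 of a 28-day cycle. Assume that this means 1 g per ticked day (no frequency is given) and that the cycle continues. The total is then 3 + 21 = 24 g at postoperative day 21. Dosing resumes on day 29, and day 47 is the 19th dosing day of the second cycle, so the total is 24 + 19 = 43 g, just past the 42 g that the Introduction mentions. The cited rate therefore serves as a marker of scale, neither a forecast nor a figure to dismiss.

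**The case against.** The strongest objection is that the consensus is not among the documents. The misfit is read from its title, and it may contain general grading by required management that would extend to medical events. That limit stands: the documents show that the stated scope does not fit, not that the consensus cannot grade neuropathy. It does not remove the point, because the protocol names no other scale and the sponsor can check the consensus at once.

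A second objection is that safety reviewers will not depend on the grade alone. Each record must describe the event, its symptoms, timing, duration, measures taken and outcome, and serious events are reported within 24 hours. This also stands. The review is weakened, not disabled.

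A reader might infer more than the documents support:

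- *That a main indicator cannot be measured.* The indicator is incidence, not the distribution of severity, and the causality criteria still allow it to be counted.
- *That about 98% of the treatment period lies outside the instrument's reach* (1 − 30/1825). This treats 30 days as the limit of complication assessment, but Secondary outcomes adds assessments at 60 days and 5 years.
- *That the consensus and Clavien–Dindo conflict for surgical events.* One, by its title, gives diagnostic criteria and the other ranks by impact and management, so they can complement each other.
- *That the plan names a range of drug toxicities.* Peripheral neuropathy is the only specific metronidazole toxicity named. Other side effects are mentioned generically, and drug hypersensitivity appears only as a non-study-related complication.
- *That late events would be recorded as minor.* Nothing in the text establishes a direction of error.

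**Conclusion.** The concern holds in a limited form. The Safety section makes an explicit choice of standard for the nature and severity of all adverse events over roughly 61 months. By its stated scope, that standard does not suit drug toxicity. Because the choice is written down, it is not a detail left to a fuller protocol or analysis plan.

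The consequence is likely inconsistency in event definitions and severity grades for late drug toxicity, and so a weaker basis for the tolerability conclusion and the 3-monthly safety review. The efficacy analysis is untouched, and the incidence of drug-related events can still be computed.

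The size cannot be fixed from the documents. About 27 of 150 patients with neuropathy is an illustration that assumes the cited 17.9% carries over to this regimen, which the plan disputes. The conclusion rests on one further assumption: that the content of the consensus matches its title. The point should be corrected because the remedy is cheap and safety is a declared main indicator, but it does not call the trial's design into question.

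**What to change.** In the Safety section, name one version of a general drug-toxicity scale for adverse-event terms and severity. CTCAE is one example; the documents do not compel that choice. Include the peripheral neuropathy terms and apply the scale at the visits already in Table 2. State that any-grade events, grade 3 or higher events, and neuropathy will be reported by arm.

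Keep the surgical consensus and Clavien–Dindo for surgical complications at all the times in Secondary outcomes: 30 days, 60 days and 5 years. Restricting them to the first 30 days would remove assessments that the plan already intends. The causality and seriousness criteria can stay as they are.

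The cost is protocol and CRF wording and brief site training. No visit or procedure is added, and no dose or clinical rule changes.
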